#### Power calculation

2.3.8

Sample size was determined using the primary objective of CA2 to determine which baseline factors are significantly associated with the decision to breastfeed among postpartum WLHIV. Assuming that the proportion of WLHIV who breastfeed is 150 among 450 recruited participants and a 5% loss to follow-up rate, we calculated that the minimum detectable odds ratio (MDOR) for detecting an association between breastfeeding and continuous exploratory variables would be 1.34 for each 1 standard deviation increase (with 80% power and a significance level of 0.05 for a two-sided test). For a binary explanatory variable with a Binomial distribution where π = 0.5, the MDOR is 1.75 (86, 87). Since the analysis uses logistic regression to evaluate associations between baseline factors and a binary outcome, the odds ratio is the natural measure of effect size. The true effect sizes of exploratory predictors are unknown *a priori*, so the MDOR provides a transparent way to quantify the smallest association that can be detected with 80% power at a two-sided *α* = 0.05, given the anticipated event rate, sample size, and predictor distribution. Thus, MDOR reflects the statistical sensitivity of the study and aligns directly with the planned modeling framework.

The co-primary objective of CA2 is to determine whether any factors are associated with the presence of detectable HIV RNA or DNA in breast milk. Because breastfeeding transmission is expected to occur rarely, if at all, in the UPLIFT study, the detection of HIV in breast milk was chosen as a proxy for the risk of transmission. Mastitis is a common complication during breastfeeding that has been associated with an increased risk of detectable HIV RNA or DNA in milk, and with HIV transmission (88–92). Mastitis was used as an example of a factor that may increase the presence of detectable HIV RNA or DNA in milk in a power calculation. Data are not available to determine the prevalence of detectable HIV RNA in milk among lactating women with HIV on integrase inhibitor-based ART; however, several studies of lactating women with HIV on nevirapine-based ART regimens demonstrated a prevalence of HIV RNA in milk of 10%–30% (93–95). We assumed that the prevalence of HIV RNA in milk would be lower among lactating women receiving modern potent ART (e.g., ∼5%). The power calculation includes the following assumptions: 1) Among participants treated with potent modern ART, up to 5% may have detectable HIV RNA in milk; 2) 10%–15% of participants who breastfeed will experience mastitis at some point during lactation; 3) in the pre-ART era, mastitis resulted in a 10-fold increase in the likelihood of detectable HIV RNA in milk (88, 89, 96, 97). If we suppose that 10%–15% of 150 participants experience mastitis and the rates of detectable HIV RNA in milk of those with and without mastitis are 50% and 5% respectively, then with a significance level of 0.05, we have 98%–99% power to detect a difference in the proportion of milk samples that contain HIV RNA between participants with and without mastitis with a sample size of 150 breastfeeding participants.

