Limitations of UPLIFT include that all study sites represent primarily urban, academic research institutions with some experience supporting WLHIV who breastfeed. The perspectives and concerns of WLHIV and healthcare staff from smaller, rural U.S. clinics and non-academic institutions may not be well represented. In addition, while rapid thematic analysis supports timely, structured synthesis of qualitative data across a large, multi-site study, this approach may limit the depth of interpretive analysis achievable with more prolonged or iterative qualitative methods. To mitigate this, analyses will be conducted by a multidisciplinary team, informed by community contributors, and will incorporate data from multiple participant groups and time points. There is the potential for social desirability and recall biases given that the interview and survey data are self-reported. The cohort study of 450 WLHIV, half of whom are expected to breastfeed, may not be large enough to identify factors associated with breastfeeding transmission of HIV, given that infant HIV acquisition is expected to occur very rarely. Therefore, we have opted to use the detection of HIV in milk samples as a proxy for the risk of transmission. Additionally, the study is observational in nature as it would not be ethical to randomize WLHIV to breastfeed or formula feed. However, repeated clinical observations and long-term follow-up of mother-infant dyads that do and do not breastfeed will enable exploration of key knowledge gaps that are unlikely to be studied otherwise in as highly rigorous of an approach.

Overall, the UPLIFT study will generate critical insights to advance patient-centered care and support informed infant feeding decision-making and management among WLHIV and HCP as U.S. institutions adapt to evolving national guidelines.

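### The detectable odds ratio of 1.75 treats one third as the unexposed-group rate, not the overall rate as worded; both quoted values are unadjusted; and the Discussion expects half, not one third, to breastfeed

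*Protocol article*

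**What the plan says.** Section 2.3.8 (Power calculation) sizes the cohort on the association between baseline factors and the decision to breastfeed. Its inputs are "Assuming that the proportion of WLHIV who breastfeed is 150 among 450 recruited participants and a 5% loss to follow-up rate", "with 80% power and a significance level of 0.05 for a two-sided test". For a continuous factor the detectable odds ratio "would be 1.34 for each 1 standard deviation increase". The binary case reads: "For a binary explanatory variable with a Binomial distribution where π = 0.5, the MDOR is 1.75". The paragraph closes by saying that "MDOR reflects the statistical sensitivity of the study and aligns directly with the planned modeling framework".

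Section 2.3.7 (Core Activity 2 quantitative analysis) describes that framework in two steps. Each baseline factor is first screened in its own marginal regression. Best-subset selection then determines which factors are significant in the regression model. The candidate list is long and includes site, demographic and clinical factors, and several social ones such as income, housing, food insecurity, interpersonal violence and substance use.

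The second paragraph of section 2.3.8, on HIV in breast milk, also uses 150 breastfeeding participants. Section 3 (Discussion) describes the cohort differently: "The cohort study of 450 WLHIV, half of whom are expected to breastfeed". Section 2.3.2 (Longitudinal cohort) also mentions about half, but there it means women who intend to breastfeed or are already doing so at enrollment.

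**The concern.** Three things in the power statement do not fit together.

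- The one third is worded as an overall proportion, but the binary figure appears to have been computed with one third as the rate in one exposure group.
- The two odds ratios carry no allowance for other covariates, and the binary one is given only for the most favourable split. The text nevertheless presents them as the sensitivity of the study and as matching the planned models.
- The expected number breastfeeding is 150 in the power section and half of 450, that is 225, in the Discussion.

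At stake is how a reader judges what the cohort can detect. No test, sample size or data collection depends on it. A reader who takes 1.75 as the sensitivity of the final models, or of an unevenly split factor, would take too favourable a view.

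**Working it through.** **Inputs from section 2.3.8.** 450 recruited; one third breastfeeding (150/450); 5% loss, so N = 450 × 0.95 = 427.5; two-sided α = 0.05; power 80%. Hence z = 1.960 + 0.842 = 2.8016. For π = 0.5 each exposure group has 427.5/2 = 213.75 women.

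**Method.** Wald test of a single logistic coefficient. For a binary factor with group rates p0 (unexposed) and p1 (exposed):

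SE² = 1/[N(1−π)p0(1−p0)] + 1/[Nπ p1(1−p1)], and power = Φ(ln OR / SE − 1.960).

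**1. Reproducing the continuous value.** For a standard normal predictor, with the information obtained by numerical integration, the detectable odds ratio is 1.343 if one third is the rate at the mean of the predictor and 1.344 if it is the overall rate. The simpler closed form exp(2.8016/√(427.5 × 2/9)) gives 1.333. The stated 1.34 is confirmed on either reading.

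**2. Reproducing the binary value, with one third in the unexposed group.** At OR 1.75 the exposed odds are 0.5 × 1.75 = 0.875, so p1 = 0.875/1.875 = 0.467.

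- SE² = 1/(213.75 × 0.2222) + 1/(213.75 × 0.2489) = 0.02105 + 0.01880 = 0.03985, so SE = 0.1996.
- ln 1.75 / SE = 0.5596/0.1996 = 2.803; power is 80%.
- Solving for exactly 80% gives 1.749, the stated 1.75.
- The implied overall rate is (0.333 + 0.467)/2 = 0.40, that is 180 of 450 and not 150.

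**3. One third as the overall proportion, as worded.** Solving for group rates that average one third at OR 1.75 gives p0 = 0.272 and p1 = 0.395.

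- SE² = 0.02364 + 0.01958 = 0.04322, so SE = 0.2079.
- ln 1.75 / SE = 2.692; power = Φ(2.692 − 1.960) = 77%.
- The detectable odds ratio at 80% power is 1.79 (Wald) or 1.78 (two-proportion z-test).

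**4. Allowance for other covariates.** The document gives no R² between a factor and the other covariates, so 0.1 to 0.3 is an assumption. The effective N is 427.5 × (1 − R²). For π = 0.5:

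| R² (assumed) | Detectable OR, one third unexposed | Detectable OR, one third overall | Power at 1.75, unexposed / overall |
|---|---|---|---|
| 0 | 1.75 | 1.79 | 80% / 77% |
| 0.1 | 1.80 | 1.85 | 76% / 72% |
| 0.2 | 1.87 | 1.92 | 71% / 67% |
| 0.3 | 1.95 | 2.02 | 65% / 61% |

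The continuous value rises from 1.34 to about 1.37 at R² = 0.1 and 1.43 at R² = 0.3.

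**5. Less even splits.** The document gives no prevalences, so 20% and 10% are assumptions. Unadjusted, the detectable odds ratio is about 2.0 at 20% and 2.5 at 10%, on either reading of one third. At R² = 0.3 these become about 2.3 and 3.0.

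**6. Half breastfeeding instead of one third.** With N = 427.5 and an overall rate of one half, the two quoted values become 1.32 per SD and about 1.73 for π = 0.5. Both are slightly smaller than with one third. This does not carry over to every uneven split: at an assumed 10% prevalence the unadjusted value is about 2.7 with half and about 2.5 with one third.

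**The case against.** The strongest reply is that nothing was miscalculated. One standard single-predictor method, with one third as the reference-group rate, returns both 1.34 and 1.75, and the methods references cited there may define the input that way. This stands: a reader might infer an arithmetic error in 1.75, but the evidence supports only a mismatch between an input's wording and its use. Nor is the reference-group reading the sole conceivable source. A simple formula with an overall rate of one third and all 450 women gives 1.751. That ignores the stated 5% loss, however, and gives 1.32 rather than 1.34 for the continuous factor, so it is the less likely origin.

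Second, the plan does contain one-factor regressions, and the quoted values describe exactly those. The sentence on alignment can also be read as explaining why an odds ratio suits logistic models. Both points are fair. They still leave the second step uncovered, and that step decides which factors are significant.

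Third, π = 0.5 is disclosed in the same sentence as 1.75, and the document gives no prevalence for any social factor. So it does not support saying that those factors are uncommon, that only odds ratios of 2 to 3 are detectable for them, or that null results will be misread. The figures for uneven splits and for R² are illustrations under stated assumptions.

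Fourth, a reader might take the gap between one third and half as a weakness in power. It is not one for the quoted values, because one third is the more cautious input. The statement in section 2.3.2 concerns intention or feeding at enrollment and can coexist with 150 who breastfeed; the Discussion's statement about expected breastfeeding cannot.

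**Conclusion.** The point holds as a matter of accurate statement. The value 1.34 is correct. The value 1.75 is correct for a reference-group rate of one third; for the overall proportion that the text states it should be 1.78 to 1.79, and power at 1.75 is about 77%. That shift of 0.03 to 0.04 is small.

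The claim of direct alignment with the planned models is overstated. Both values assume one unadjusted predictor. Under an assumed R² of 0.1 to 0.3 the evenly split value is about 1.80 to 2.02, and under an assumed prevalence of 20% or 10% the unadjusted value is about 2.0 or 2.5. The direction is certain; the size depends on those assumptions.

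The 150 in section 2.3.8 and the half in the Discussion contradict each other and need to be reconciled. None of this shows that the study is underpowered or that its sample size is wrong.

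**What to change.** Text changes only:

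- In section 2.3.8, restate the binary value as about 1.79, or keep 1.75 and say that one third is the rate in the unexposed group.
- Label 1.34 and 1.75 (or 1.79) as values for a single unadjusted predictor.
- Replace the sentence on alignment with one saying that adjusted models and less evenly split factors have larger detectable odds ratios. Give a short range with its assumptions, for example R² from 0 to 0.3 and prevalence from 10% to 50%.
- Use one expected number breastfeeding in both parts of section 2.3.8 and in the Discussion. If the Discussion meant intention at enrollment, say so there.

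The cost is a few sentences and slightly less favourable stated figures. Design, sample size and analysis are unchanged.

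### The 98%–99% mastitis power rests on group rates that imply about twice the plan's own 5% ceiling; at 5% overall it is about 83%–86%

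*Protocol article*

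**What the plan says.** Section 2.3.8 (Power calculation) uses mastitis as the worked example for the objective on factors associated with detectable HIV in breast milk. It lists three assumptions:

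- Prevalence: "Among participants treated with potent modern ART, up to 5% may have detectable HIV RNA in milk". The rationale just before the list gives the same figure, about 5%, for lactating women on modern ART.
- Exposure: "10%–15% of participants who breastfeed will experience mastitis at some point during lactation".
- Effect: a 10-fold increase in the likelihood of detectable RNA with mastitis, taken from the pre-ART era.

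The calculation then supposes that "10%–15% of 150 participants experience mastitis" and that "the rates of detectable HIV RNA in milk of those with and without mastitis are 50% and 5% respectively". It concludes: "we have 98%–99% power to detect a difference in the proportion of milk samples that contain HIV RNA", "with a sample size of 150 breastfeeding participants". No test is named. Sidedness is not given for this calculation; the other calculation in the same section is specified "with 80% power and a significance level of 0.05 for a two-sided test".

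**The concern.** The 5% is introduced as an upper limit for all treated participants and is nowhere restricted to women without mastitis. The calculation uses it as the rate in women without mastitis and adds a mastitis group at 50% on top. A figure for the whole cohort has become the figure for the lower-risk part of it, so both group rates, and the gap between them, are larger than the stated prevalence allows.

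This is the only power figure given for the milk objective. The plan treats HIV in milk as its proxy for transmission risk, and the Discussion expects the results to inform guidance on breastfeeding complications. If no mastitis association is found, the stated power is the yardstick for how much that absence means, and a yardstick of 98%–99% would lend it more weight than the plan's own prevalence supports.

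**Working it through.** **Inputs, all from section 2.3.8.** N = 150 breastfeeding women. Mastitis share m = 10%–15%, that is 15 vs 135 women up to 22 vs 128 or 23 vs 127 (22.5 rounded either way). Alpha is 0.05, taken as two-sided by analogy with the other calculation in the section. Rates are 50% and 5%, the overall ceiling is 5%, and the ratio is 10.

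**Step 1: reproduce the stated figure.** For 50% vs 5%:

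| Groups | Fisher exact (enumerated) | Pooled normal |
|---|---|---|
| 15 vs 135 | 98.8% | 98.8% |
| 22 vs 128 | 99.8% | 99.8% |
| 23 vs 127 | 99.9% | 99.8% |

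The stated 98%–99% is reproduced to within about a point.

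**Step 2: overall prevalence implied by those rates.** Overall = (n1 × 0.50 + n0 × 0.05) / 150, where n1 and n0 are the numbers with and without mastitis.

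- 15 vs 135: (7.5 + 6.75) / 150 = 9.5%
- 22 vs 128: (11 + 6.4) / 150 = 11.6%
- 23 vs 127: (11.5 + 6.35) / 150 = 11.9%

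The ceiling is 5%. Put the other way, at 10% mastitis a 50% rate contributes 0.10 × 0.50 = 5% by itself, leaving 0% for everyone else. At 15% it contributes 7.5%, already above the ceiling.

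**Step 3: rates consistent with 5% overall and a 10-fold ratio.** Solve (1 − m) × p0 + m × 10 × p0 = 0.05, so p0 = 0.05 / (1 + 9m) and p1 = 10 × p0.

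- m = 15/150: p0 = 0.05 / 1.90 = 2.63%, p1 = 26.3%
- m = 22/150: p0 = 0.05 / 2.32 = 2.16%, p1 = 21.6%
- m = 23/150: p0 = 0.05 / 2.38 = 2.10%, p1 = 21.0%

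**Step 4: power at the consistent rates, N = 150.**

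| Overall prevalence | Fisher, 15 / 22 / 23 with mastitis | Pooled normal, same order |
|---|---|---|
| 5% | 82.6% / 83.8% / 85.1% | 85.4% / 85.9% / 85.9% |
| 4% | 73.3% / 73.3% / 74.9% | 78.9% / 79.3% / 79.2% |
| 3% | 60.8% / 58.0% / 59.7% | 70.5% / 70.6% / 70.5% |
| 2% | 43.2% / 38.3% / 39.7% | 59.9% / 59.3% / 59.1% |

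Only 0.05 × 150 = 7.5 positives are expected at the ceiling, and fewer below it, so the exact figures are the safer guide. The choice of test matters: at 5%, an exact uncorrected chi-square gives about 87%–90% and a continuity-corrected normal formula about 77%–79%. None of the methods tried reaches 98%.

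**The case against.** The strongest defence is that 5% was meant as a background rate per milk sample. The comparison is worded in terms of milk samples, and if mastitis is brief, the rate in samples taken outside an episode would be close to the overall rate; ten times that is 50%. This reading is possible, but the text does not establish it. The 5% is stated for participants, and mastitis is counted if it occurs at any time in lactation. If this is what was meant, a clarifying sentence is needed.

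It is also fair to say that the calculation is conditional and open about its two rates, that mastitis is offered as an example, and that the cohort size was set on the feeding-decision objective. The Discussion expects half of 450 women to breastfeed; with 225 instead of 150, Fisher power at 5% overall would be about 93%–95%. But section 2.3.8 plans on 150, and the claim should hold on that basis.

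A reader might be tempted by four stronger readings that the documents do not support:

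- *The power was miscalculated.* It was not; 50% vs 5% gives the stated figure.
- *The three listed assumptions are mutually incompatible.* They are not; 26.3% vs 2.63% with 10% mastitis satisfies all of them. The conflict is between the first assumption and the 50% and 5% rates.
- *The study is underpowered for this objective.* At the 5% ceiling, power is still above 80% by Fisher and pooled normal.
- *Power is far lower because episodes go unsampled or the mastitis effect is weaker under modern ART.* Either may happen, but the documents give no figure for the share of episodes sampled or for a smaller ratio. The plan also provides for complication visits, prompt reporting of breast symptoms, milk collection at each visit, and a mixed model over repeated samples that a one-outcome-per-woman calculation does not represent.

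**Conclusion.** The concern holds as an inconsistency of inputs. The group rates used imply about 9.5%–12% overall, roughly twice the plan's ceiling. If the 5% is taken as written, as an overall rate, 98%–99% should read about 83%–86%, an overstatement of some 12–16 points at the ceiling. Below the ceiling the shortfall grows: by Fisher, power is already under 80% at 4%.

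This rests on a two-sided 0.05 test, 10-fold read as a risk ratio, one outcome per woman, every mastitis case counted as exposed, and no loss from the 150. Read as an odds ratio, 10-fold gives about 73%–80% by Fisher at 5% overall. The point should be fixed, but it does not put the design in question.

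**What to change.** State whether 5% is the overall rate or the rate in women without mastitis, and derive both group rates from that choice.

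- **If overall:** replace 98%–99% with about 83%–86% at the ceiling, name the test and its sidedness, and add a short table of power at lower prevalences (for example 4%, 3% and 2%).
- **If without mastitis:** correct the first assumption accordingly and state the implied overall prevalence of about 9.5%–12%. The 98%–99% can then stand, with the test named.

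A smaller mastitis ratio or incomplete sampling of episodes may be added as sensitivity scenarios, provided they are labelled as assumptions and the group rates are solved again for each scenario.

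The cost is rewording one paragraph and adding a small table. Sample size, visits and analysis are unchanged; under the overall reading the published power becomes less favourable.

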#### Qualitative and mixed methods analysis

2.3.9

IDIs conducted in CA2 build on themes identified in CA1 and are analyzed using the same rapid thematic analysis approach. Across CA1 and 2, qualitative data from IDIs are summarized using matrix-based methods to identify key themes, patterns, and changes over time related to infant feeding decision-making, experiences, and care needs among WLHIV and other influential individuals.

UPLIFT uses a convergent mixed-methods analytic approach in which qualitative and quantitative data are analyzed separately and then integrated (Figure 4). We will integrate qualitative and quantitative findings through a joint display table, which will align themes from in-depth interviews (CA1) with corresponding quantitative measures and trends (CA1 and CA2). This joint display is used to identify areas of convergence, divergence, and expansion, allowing comparison of lived experiences and perspectives with observed quantitative patterns over time. This mixed-methods integration supports a comprehensive and contextualized understanding of infant feeding decisions, practices, and care needs among pregnant and postpartum WLHIV in the U.S.

**Figure 4 F4:**
[figure not shown]
Convergent mixed-methods analysis approach for UPLIFT. Qualitative and quantitative data will be analyzed separately and then integrated in a convergent mixed-methods analysis. BF, breastfeed; CEA, Cost Effectiveness Analysis; WLHIV, women living with HIV.

#### Cost and cost-effectiveness analyses

2.3.10

An economic evaluation will be conducted to estimate the cost and cost-effectiveness of infant feeding strategies for WLHIV following the recommendations of the Second U.S. Panel for Cost-effectiveness in Health and Medicine (98). We will employ a societal perspective and use a micro-costing approach to estimate provider costs for each feeding strategy. In addition, we will incorporate participant costs and potential productivity losses from labor market participation or household production as components of overall cost. This analysis is descriptive in nature and is intended to characterize the range and distribution of costs associated with each infant feeding strategy rather than to evaluate differences by employment status or workplace factors. We will calculate mean total costs for each mother/infant dyad for breastfeeding and replacement feeding and examine variation in cost components by infant feeding strategy. Cost data will be collected through self-administered participant surveys (Supplementary Table) and time and motion studies to estimate labor and participant time costs. Labor costs will be calculated using labor time (hours spent on infant feeding activities) and national wage rates and fringe benefits by job classification. Participant survey data will be used to characterize patient costs including expenses for infant feeding as well as time spent on infant feeding activities and associated losses in productivity. All CA2 participants will complete cost surveys at 6, 20, and 48 weeks. The time and motion evaluations will be conducted at a subset of sites, selected based on accrual projections and services offered. Cost data elements that will be used to estimate and compare the costs associated with breastfeeding and replacement feeding for mother/infant pairs are detailed in the cost inventory (Table 4).

**Table 4 T4:** Proposed cost inventory by infant feeding strategy.

Cost Category	Breastfeeding	Replacement Feeding
Program Delivery Costs	Breastfeeding support and monitoring (e.g., lactation support, counseling follow-up visits medication)	Infant feeding support and monitoring (counseling, follow up visits, medication)
Materials and Supplies	Consumables, educational materials	Consumables Educational materials
Program Administrative and Costs	Labor costs for supervision, overhead	Labor costs for supervision, overhead
Patient Direct Costs	Out-of-pocket feeding costs, breast pumps & accessories, bottles, storage supplies	Out-of-pocket feeding costs, formula, bottles, sterilization supplies
Patient Time Costs and Productivity Losses	Patient time spent breast feeding and attending feeding-related medical visits	Patient time spent replacement feeding and attending feeding-related medical visits
Averted Health Care Costs	Averted medical care costs attributable to breast feeding	Averted medical care costs attributable to formula feeding

We will use decision analytic modeling using a Markov model to extend the analysis and estimate the incremental cost per quality-adjusted life year (QALY) of breastfeeding compared with replacement feeding (99, 100). The model will incorporate infant and maternal morbidity and mortality, as well as HIV transmission and averted illness by infant feeding strategy. It will be parameterized with UPLIFT study data and data from the published literature including the 2025 Agency for Healthcare Research and Quality (AHRQ) systematic review of breastfeeding-related health outcomes in infants and children (101). We will explore uncertainty in the incremental cost-effectiveness ratio (ICER) with sensitivity analyses accounting for plausible variation in applicable cost and outcome parameters.

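### Mean costs by self-selected feeding method, labelled descriptive, are extended to an incremental cost per QALY with no stated control of confounding

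*Protocol article*

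**What the plan says.** Protocol article, Section 2.3.10 (Cost and cost-effectiveness analyses):

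- The cost estimator is a group mean: "We will calculate mean total costs for each mother/infant dyad for breastfeeding and replacement feeding".
- Overall cost includes "potential productivity losses from labor market participation or household production as components of overall cost".
- On purpose: "This analysis is descriptive in nature", meant to show the range and distribution of costs for each strategy "rather than to evaluate differences by employment status or workplace factors".
- The cost inventory (Table 4) is nevertheless to be used to "estimate and compare the costs associated with breastfeeding and replacement feeding for mother/infant pairs".
- A Markov model then extends the analysis to "estimate the incremental cost per quality-adjusted life year (QALY) of breastfeeding compared with replacement feeding". On its inputs: "It will be parameterized with UPLIFT study data", together with published literature.
- Uncertainty in the ratio is to be explored by varying cost and outcome parameters over plausible values. No other safeguard is named.

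Elsewhere in the article, Section 2.3.7 lists site, education, employment, income and housing among the baseline factors to be examined as predictors of feeding type. The limitations paragraph of the Discussion confirms that feeding is not randomized.

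**The concern.** An incremental cost per QALY says what would change if one feeding strategy replaced the other. A difference between the mean costs of two groups of women who chose their own method answers that question only if the groups are otherwise comparable in whatever drives cost. The article treats several cost drivers as possible reasons for the choice itself. Employment is the clearest: it may predict feeding, and it bears directly on labor-market productivity loss, which is part of the cost.

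Calling the first step descriptive is reasonable for the first step. The label does not carry over to a ratio built on it. Varying a cost input around a confounded centre widens the range shown but leaves the centre where it is.

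Cost-effectiveness is a stated secondary objective of Core Activity 2 (Table 3), and the Discussion says the findings will inform practice and policy. A biased incremental cost could move the ratio in either direction.

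**Working it through.** **1. What can be reproduced.** The article gives no cost, QALY or cost-effectiveness figure, so the plan has no number of its own to reproduce on this point. The structural part is settled by reading. Section 2.3.7 names regression models for the association of feeding method with maternal mental health, quality of life, decision regret, satisfaction and infant growth and development. Cost is not in that list. For cost, Section 2.3.10 names group means and then the Markov model.

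**2. A benchmark for imbalance.** Section 2.3.8 gives a minimum detectable odds ratio of 1.75 for a binary factor with prevalence 0.5, assuming 150 of 450 women breastfeed and 5% are lost. With n = 450 × 0.95 ≈ 428, a two-proportion calculation (80% power, two-sided 0.05) gives:

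- 1.74 if one third is the breastfeeding rate in women without the factor;
- 1.78 if one third is the overall rate.

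The stated 1.75 is therefore about right and can serve as a benchmark.

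**3. Convert it to group shares.** Let p0 and p1 be the probabilities of breastfeeding without and with the factor. Solve 0.5·p0 + 0.5·p1 = 1/3 with p1/(1 − p1) = 1.75 × p0/(1 − p0). This gives p0 = 0.272 and p1 = 0.395.

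- Share with the factor among breastfeeding women: 0.5 × 0.395 / (1/3) = 59.2%.
- Share among replacement-feeding women: 0.5 × (1 − 0.395) / (2/3) = 45.4%.
- Imbalance: 13.9 points.

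The study has about 80% power to detect an imbalance of this size. Smaller ones could go unflagged and still shift mean costs.

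**4. Effect on incremental cost.** Suppose cost per dyad differs by D between the two factor levels, whatever the feeding method. The difference in raw means then carries a spurious 0.139 × D. Both D and the QALY gain below are assumptions.

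| Assumed D | Spurious incremental cost | Shift in ratio, QALY gain 0.10 | Shift in ratio, QALY gain 0.01 |
|---|---|---|---|
| $1,000 | $139 | about $1,390 per QALY | about $13,870 per QALY |
| $5,000 | $693 | about $6,930 per QALY | about $69,350 per QALY |
| $10,000 | $1,387 | about $13,870 per QALY | about $138,700 per QALY |

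**5. Productivity loss alone.** Assume 60% of one group and 45% of the other are employed. If only employed women lose productivity, the ratio of mean loss is 0.60/0.45 = 1.33. Section 2.3.10 also counts household production, so let a non-employed woman's loss be a fraction h of an employed woman's. The ratio becomes (0.60 + 0.40h)/(0.45 + 0.55h):

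- h = 0: 1.33
- h = 0.25: 0.700/0.5875 = 1.19
- h = 0.5: 0.80/0.725 = 1.10
- h = 1: 1.00

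The 33% gap is thus an upper end for these shares (with h between 0 and 1). It concerns part of one of the six cost categories in Table 4.

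**The case against.** The strongest reply is that much of this is inference. A reader might conclude that the plan commits to unadjusted means and places them directly in the Markov model. The article says neither. It condenses a full protocol that is not shown, and adjustment of cost inputs could be specified there or in an analysis plan. It also does not say which model parameters come from study data and which from literature. This stands, and it limits the point to a risk in the plan as written.

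Second, the descriptive sentence, read in full, mainly says that comparing employment subgroups is not an aim. It does not say that employment will be ignored when the strategies are compared. That also stands. The point does not depend on the sentence; it depends on the step from group means to an incremental ratio.

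Third, a reader might infer that wage and income differences pass straight into the ratio. Labor time is to be valued at "national wage rates and fringe benefits by job classification", which takes local wage variation out of staff labor. Whether the same rates apply to participants' own time is not stated. The wage and income route is therefore weaker than the employment route.

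Fourth, whether employment or any other factor differs between the feeding groups is something the study will find out. That is correct.

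What the reply does not meet is this: the article names an estimator for cost, extends it to a causal-type contrast between self-selected groups, and offers only parameter variation as protection.

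**Conclusion.** The point holds as a risk. Followed as written, Section 2.3.10 can yield a confounded incremental cost, because it moves from mean costs by chosen feeding method to an incremental cost per QALY without stating how baseline differences will be handled. Employment through productivity loss is the best-supported route. Site, education, income and housing are further candidates, acting mainly through participant productivity and out-of-pocket costs.

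The documents do not support saying that such differences do enter the ratio, or by how much. The dollar figures rest on an assumed cost difference, an assumed QALY gain and an imbalance set at the plan's own minimum detectable odds ratio. The 33% figure rests on assumed employment shares and on zero household-production loss in non-employed women. The matter affects one secondary objective and leaves the co-primary analyses and the sample size untouched. It still merits a change, because the remedy is cheap and better than the stated group means for this purpose.

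**What to change.** Keep the raw mean costs by feeding method as the descriptive result. For the participant-level survey costs that feed the Markov model (out-of-pocket, time and productivity):

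- fit a cost regression, for example gamma with log link, on feeding strategy, site and the entry covariates already collected (employment, income, education, parity, housing);
- average its predictions under each strategy over the whole cohort, so that both means refer to the same women;
- attach intervals by bootstrap;
- report the cost-effectiveness ratio with raw and with standardised inputs side by side.

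Use covariates measured at entry, because later changes in employment may themselves result from the feeding method. Leave staff labor out of this regression. The time-and-motion work covers only a subset of sites, so a site-adjusted model cannot be fitted to it for every dyad; treat those results as unit costs. Section 2.3.10 should also state which model parameters come from study data and in what form.

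The cost is a little more analysis work and some dependence on the regression model, which the side-by-side report makes visible. For the survey costs no new data are needed.
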